## Abstract

**Background:**

The US cancer survivor population is projected to hit 26M by 2040. Chemotherapy is an effective cancer treatment, but can diminish cancer survivors’ quality of life—particularly cognitive function—through select pathophysiological processes, including immune system and antioxidant dysregulation. The resulting cytokine release can impair cerebrovascular function—likely contributing to chemotherapy-induced cognitive impairment (CICI; “chemo-brain”). Type 2 diabetes mellitus (T2DM)—a common cancer survivor comorbidity—shares underlying pathophysiology with CICI. Cancer survivors with T2DM might thus have a higher CICI risk than those without T2DM. Physical activity (PA) counteracts CICI’s and T2DM’s pathophysiology, but little to no research has been conducted assessing the impact of PA on this joint pathophysiology.

**Objective:**

To compare cerebrovascular and cognitive function as well as proinflammatory, cardiometabolic, epigenetic, and psychosocial outcomes between ancer survivors with and without T2DM pre- to postengagement in a 12-week technology-based PA program grounded in the Social Cognitive Theory. We hypothesize that cancer survivors with and without T2DM will demonstrate similar pre to poststudy improvements in psychosocial outcomes, but that changes in cerebrovascular and cardiometabolic outcomes, as well as PA engagement, will be greater for cancer survivors with T2DM. We also believe that each group will have distinct epigenetic profiles that will change pre to poststudy.

**Methods:**

We are conducting a 30-participant pilot study in cancer survivors with (n=15) and without (n=15) T2DM—all of whom report currently experiencing “chemo-brain.” To account for attrition, we are recruiting 38 cancer survivors from Oklahoma City, OK, and the surrounding area. Among the most important eligibility criteria are the self-report of cognitive difficulties following primary cancer treatment, being ≥18 years old, being within 3 years of primary cancer treatment, and not meeting nationally recommended PA guidelines. Participants receive 2 smartphone apps. One smartphone app provides health education and the ability to set goals and journal about their wellness journey. The other provides a workout program continually tailored to each participant via their communication with the study exercise physiologist, with resistance bands and a wearable device provided to support the program. At Baseline and Poststudy, we assess cerebrovascular function (transcranial doppler [TCD]), cognition (National Institutes of Health Toolbox), cardiometabolic outcomes (venipuncture), and epigenetics (saliva collection). Participants also wear accelerometers at Baseline and Poststudy to objectively assess PA, with Baseline, Midpoint, and Poststudy surveys assessing psychosocial outcomes. We will use *t* tests and chi-square tests to assess baseline differences and repeated-measures ANCOVA to assess changes over time.

**Results:**

Participant recruitment started in March 2025, and we expect to recruit until late 2026. We will begin analyzing baseline data in 2026.

**Conclusions:**

Successful study completion will provide valuable insights into the remote delivery of PA-oriented supportive care for cancer survivors experiencing chemo-brain, as well as how T2DM and PA contribute to the mechanistic underpinnings of chemo-brain.

**Trial Registration:**

ClinicalTrials.gov NCT06725953; https://clinicaltrials.gov/study/NCT06725953

**International Registered Report Identifier (IRRID):**

DERR1-10.2196/79739

## Introduction

### Background

While incident cancer cases of any site remain stable, 5-year cancer survival rates have increased [1]. In January 2022, >18M individuals in the US were cancer survivors—defined here as those diagnosed with cancer onward [2]—with a projected increase to 26M by 2040 [3]. Although modern cancer treatments are effective, these treatments can worsen cancer survivors’ health-related quality of life (HRQoL) [4-6]. Several cancer treatments—most notably, chemotherapy—are associated with cognitive difficulties [7-9]. While chemotherapy effectively treats many malignancies, it also negatively impacts vascular endothelial cells [10-12]—leading to pathophysiological processes contributing to cancer survivors’ often-reported chemotherapy-induced cognitive impairment (CICI; aka “chemo-brain”) during/after treatment [7,8]. As the number of cancer survivors increases, CICI mitigation research is crucial to improve HRQoL.

CICI likely occurs for several reasons. Chemotherapy can induce immune and antioxidant dysregulation [13-16]. This dysregulation can lead to peripheral proinflammatory cytokines being released, which damage and cross the blood-brain barrier [13,14,17]—contributing to central proinflammatory cytokine release [18-21] and causing neuroinflammation-related impairments in the myelination process [22]. Endothelial dysfunction and cerebral autoregulation failure can also result from this damage [12,23-25]. Reviews [10,11] suggest these mechanisms alter cerebrovascular function more broadly by impairing cerebral perfusion, glucose metabolism, and angiogenesis; thus contributing to CICI.

Type 2 diabetes mellitus (T2DM) is both a risk factor for developing several common cancers and, given its prevalence, a common cancer survivor comorbidity [26,27], heightening cancer recurrence risk [28,29]. Several pathophysiological mechanisms underlying CICI are observed with T2DM [30]. Insulin resistance can result in repeated hyperglycemic episodes and subsequent proinflammatory cytokine elevation [31-35]—possibly explaining why insulin resistance is correlated with diminished cerebrovascular and cognitive function in individuals with T2DM but without cancer [36-38]. This might also explain why, in newly diagnosed cancer survivors with proinflammatory comorbidities (eg, T2DM), higher proinflammatory cytokines and poorer cognitive function have been observed relative to cancer survivors without comorbidities—even prior to chemotherapy [39]. CICI mitigation research that compares those with and those without T2DM may help clarify the magnitude to which T2DM contributes to the mechanisms underlying CICI. Notably, CICI mitigation research may also benefit from the inclusion of assessments of the epigenome, given that upregulated proinflammatory cytokines, a hallmark of chemotherapy and T2DM, may lead to changes in DNA methylation via histone modification [21,40,41].

Aerobic physical activity (PA) and resistance training (RT) have robust health benefits counteracting much of the pathophysiology underlying CICI and T2DM [42,43]. Reviews [44,45] suggest better cerebrovascular function in those who are more active or fitter relative to those who are less active or fit, with greater fitness positively associated with cognitive function in other at-risk populations [46,47]. In those with T2DM, research has shown that PA is impactful at lowering proinflammatory cytokines [42,48-50] and improving insulin sensitivity [51,52]. Yet, research is needed on how increasing PA in cancer survivors with T2DM reporting CICI improves cerebrovascular and cognitive health through improved fitness. Notably, cancer survivors prefer supportive, individualized, home-based PA programming that includes RT and aerobic activities such as walking [53]. Home-based programs are recommended by the American Cancer Society [54] given their ability to circumvent some of the barriers to PA program participation (eg, distance to clinic, lack of time) among those living with and beyond cancer. Smartphone app technology can assist in providing this home-based PA program access. Relative to routine care, smartphone app–based supportive care among cancer survivors has been observed to improve HRQoL, self-efficacy, and symptoms of distress and depression [55]. Further, multicomponent interventions that include personalized PA programming delivered via smartphone apps, with wearable devices to supplement behavior change, have shown promise for increasing PA among cancer survivors [56,57].

We are conducting a 30-participant pilot study in cancer survivors with T2DM (n=15) and without T2DM (n=15)—all self-reporting “chemo-brain”—that includes personalized PA programming and education delivered via 2 smartphone apps, with a wearable device provided for further behavior change support. We have detailed our Specific Aims and Hypotheses below.

### Specific Aim 1

Characterize cerebrovascular function, cognitive function, proinflammatory cytokines, and cardiometabolic outcome differences between cancer survivors with and without T2DM. We hypothesize that cancer survivors with T2DM will have (1) poorer measures of middle cerebral artery velocity and cerebrovascular conductance, reactivity, and resistance; (2) lower executive function scores; (3) higher C-reactive protein, interleukin-6, and monocyte chemoattractant protein 1 concentrations; and (4) higher blood pressure and insulin resistance.

### Specific Aim 2

Examine pre- to post-PA program differences for changes in Specific Aim 1’s outcomes between cancer survivors with and without T2DM. We hypothesize that greater pre- to post-PA program improvements in these outcomes will be observed for cancer survivors with T2DM.

### Specific Aim 3

Assess pre- to post-PA program differences for changes in Social Cognitive Theory–based (SCT-based) [58,59] constructs, select psychosocial outcomes, HRQoL, and PA between cancer survivors with and without T2DM. We hypothesize that cancer survivors with and without T2DM will demonstrate pre- to post-PA program improvements in (1**)** SCT-based, PA-related self-efficacy, outcome expectations, enjoyment, social support, and barriers; (2) stress, anxiety, mood, and depressive symptoms, and that cancer survivors with T2DM will have greater improvements than cancer survivors without T2DM; (3) in HRQoL due to greater improvements in physical functioning as well as pain intensity/interference, and (4) overall PA participation due to greater increases in light and moderate PA.

### Exploratory Aim

Characterize epigenetic profiles of biologically relevant pathways related to neurocognition, energy metabolism, and proinflammatory processes in cancer survivors with and without T2DM, and whether changes are observed in these profiles pre- to post-PA program. We hypothesize that distinct epigenetic profiles will be evident between groups but that both groups will show pre- to post-PA program changes in these profiles.

## Methods

### Study Design and Recruitment

We are conducting a National Institutes of Health Stage 1 trial [60], and we have registered this trial on ClinicalTrials.gov (NCT06725953). Moreover, we used the SPIRIT (Standard Protocol Items: Recommendations for Interventional Trials)-Outcomes Guidelines to guide the construction of this manuscript [61]. We are recruiting individuals within Oklahoma City and the greater state of Oklahoma. Our accrual target is 38 participants to allow our desired number of 30 participants to be achieved when accounting for an anticipated 20% attrition rate [62]. We are conducting rolling recruitment and are recruiting via (1) emailed and posted flyers; (2) digital advertising to local survivorship groups; (3) oncologist referral; and (4) chart reviews/assistance from the Stephenson Cancer Center Clinical Trials Office. Potentially eligible individuals are sent a REDCap-based (Research Electronic Data Capture–based) screening survey, and, whenever possible, we are verifying cancer diagnosis, chemotherapy regimen, and T2DM status via medical records. We are evaluating individuals against stringent eligibility criteria. Specifically, our inclusion criteria are as follows: (1) 18 years or older; (2) ability to speak/read English; (3) ability to provide informed consent; (4) underwent treatment within the last 3 years for a non–brain-related cancer with said treatment having included chemotherapy and not currently undergoing any active cancer treatments (ongoing endocrine/hormonal therapy or immunotherapy, when either are used for maintenance purposes, are acceptable); (5) self-reported cognitive difficulties following cancer treatment; (6) (for cancer survivors with T2DM) current T2DM diagnosis as classified by a fasting blood glucose of ≥126 mg/dL, 2-hour oral glucose tolerance test of ≥200 mg/dL, HbA_1c_ level of ≥6.5%, or use of medications (eg, Metformin) or insulin to treat hyperglycemia or (for cancer survivors) no current T2DM diagnosis as classified by a fasting blood glucose <100 mg/dL, 2-hour oral glucose tolerance test <140 mg/dL, or HbA_1c_ level of <5.7%. Presence/absence of T2DM to be confirmed preferentially via physician’s documentation or via our measurement of participants’ fasting blood glucose during the blood draws within Part 2 of Baseline Testing (Figure 1); (7) own smartphone or computer with internet access; and (8) willing to participate in the 12-week remotely-delivered PA program. Our exclusion criteria are as follows: (1) reporting a Physical Activity Readiness Questionnaire score indicating PA may be unsafe unless a doctor’s note clearing a prospective participant for study participation can be provided; (2) engaging in ≥75 min/week of vigorous-intensity PA, ≥150 min/week of moderate-intensity PA, or an equivalent combination of both over the last 3 months; (3) currently undergoing active cancer treatment or planning more treatment within the next 3 months; (4) classified within the prediabetes range for their fasting blood glucose measurement (100-125 mg/dL) during Part 2 of Baseline Testing. Notably, those with T2DM verified via a physician’s documentation and who report the use of medications or insulin to treat hyperglycemia, who are found to be in the prediabetes range, will still be enrolled within the T2DM group and study. These results would indicate a participant with well-controlled T2DM, not prediabetes; and (5) currently a prisoner, pregnant, or planning to become pregnant during the study.

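### The T2DM and non-T2DM definitions overlap when glycemic measures disagree, and the prediabetes exclusion checks fasting glucose only

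*Protocol article*

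**What the plan says.** All the relevant text is in the Protocol article, Methods, Study Design and Recruitment.

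- **T2DM group (inclusion criterion 6).** One of four criteria is enough: fasting glucose of at least 126 mg/dL, or "2-hour oral glucose tolerance test of ≥200 mg/dL, HbA_1c_ level of ≥6.5%, or use of medications" or insulin for hyperglycemia.
- **Comparison group (inclusion criterion 6).** The head term is "no current T2DM diagnosis as classified by", followed by the list "a fasting blood glucose <100 mg/dL, 2-hour oral glucose tolerance test <140 mg/dL, or HbA_1c_ level of <5.7" (percent). The list has no condition on glucose-lowering treatment.
- **Confirmation.** Presence or absence of T2DM is to be "confirmed preferentially via physician’s documentation or via our measurement of participants’ fasting blood glucose during the blood draws" at Part 2 of Baseline Testing. The recruitment text adds that "whenever possible, we are verifying cancer diagnosis, chemotherapy regimen, and T2DM status via medical records".
- **Prediabetes (exclusion criterion 4).** People are excluded if "classified within the prediabetes range for their fasting blood glucose measurement (100-125 mg/dL) during Part 2 of Baseline Testing". There is one exception: those with documented T2DM who report treatment and "who are found to be in the prediabetes range, will still be enrolled within the T2DM group and study".

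No sentence says which group applies when two measures disagree. None excludes a prediabetes-range HbA1c or OGTT when fasting glucose is normal.

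**The concern.** If any one positive result makes a person T2DM, then non-T2DM has to mean that no result is positive. A list joined by *or* on both sides cannot do this, because one person can have a positive result on one measure and a normal result on another. The comparison-group cut-offs are also set below the prediabetes range on all three measures, and exclusion 4 exists to keep prediabetes out. Yet the *or* and the fasting-only exclusion enforce that intent on a single measure.

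Group membership is not randomized. It defines the between-group comparisons in Aims 1 to 3 and the exploratory aim. The Introduction's rationale is that insulin resistance and hyperglycemia drive inflammation and poorer cerebrovascular and cognitive function, so a dysglycemic comparator carries some of the exposure under study. With 15 per group, one misplaced person is 1/15, about 7% of a group. The study is meant to supply data for planning larger trials, so a diluted contrast would pass into those plans.

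**Working it through.** **The plan's own figure.** The only sample-size figure is the accrual target: 30/(1 − 0.20) = 37.5, rounded up to 38. It reproduces, and the point does not depend on it.

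**Inputs, all from criterion 6 and exclusion 4.**

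| Measure | Normal (N) | Intermediate (P) | Diabetes (D) |
|---|---|---|---|
| Fasting glucose, mg/dL | <100 | 100–125 | ≥126 |
| OGTT, mg/dL | <140 | between | ≥200 |
| HbA1c, % | <5.7 | between | ≥6.5 |

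Glucose-lowering treatment is yes or no. This gives 3 × 3 × 3 × 2 = 54 profiles.

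**Rules as written.**
- T2DM: at least one D, or treated.
- Non-T2DM: at least one N.
- Exclusion 4: fasting glucose is P.

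**Overlap.**
- Untreated profiles: 27. Without any N: 2³ = 8. Without any D: 2³ = 8. With neither N nor D: 1. Meeting both definitions: 27 − 8 − 8 + 1 = 12.
- Treated profiles: all 27 meet the T2DM definition, and those with at least one N also meet the other: 27 − 8 = 19.
- Total meeting both: 12 + 19 = 31 of 54.
- Of these 31, 24 have fasting glucose outside 100–125 mg/dL and so are not reached by exclusion 4: 10 untreated and 14 treated.

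An untreated person with fasting glucose 95 mg/dL and HbA1c 6.6% is one of the 10.

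**Prediabetes that passes.** Three untreated profiles meet only the non-T2DM definition and pass exclusion 4 although OGTT, HbA1c or both are intermediate. Fasting glucose 98 mg/dL with HbA1c 6.2% is an example.

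**The fallback.** If status is confirmed by fasting glucose alone, every untreated profile with normal fasting glucose is confirmed as non-T2DM. There are 3 × 3 = 9 of these, and 8 have an abnormal OGTT or HbA1c.

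**After correction.** Joining the three comparison-group criteria by *and* leaves one overlapping profile: all values normal but treated. Adding a no-treatment condition brings the overlap to 0.

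**Dilution, illustrative only.** Suppose a share m of the 15 comparison participants is misclassified, and each loses a fraction k of the true difference d. The expected difference is d(1 − km). The documents give none of d, m or k. Assume d = 1.0 SD, 15 per group, and a two-sided t test at 0.05:

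| m | k = 1 (fully T2DM-like): difference, power | k = 0.5 (halfway): difference, power |
|---|---|---|
| 0 | 1.00 SD, 75% | 1.00 SD, 75% |
| 10% | 0.90 SD, 66% | 0.95 SD, 71% |
| 20% | 0.80 SD, 56% | 0.90 SD, 66% |
| 30% | 0.70 SD, 46% | 0.85 SD, 61% |

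**The case against.** The strongest reply is that the text contains a hierarchy. The comparison group is headed by absence of a current diagnosis, and physician's documentation takes precedence over study glucose. The exception to exclusion 4 treats documented, medicated people with fasting glucose of 100–125 mg/dL as well-controlled T2DM. That reasoning carries over to values below 100, although it is not written for them. A reader might infer that anyone on metformin with fasting glucose 95 mg/dL could be put in either group at will. The documents do not support that: someone with documented, treated T2DM would be placed by the documentation.

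This part stands, but it does not close the gap. The word diagnosis is itself defined by the *or* list, record verification is conditional, and the fallback is fasting glucose alone. Undiagnosed or undocumented discordant cases stay open. A chart without a T2DM diagnosis also does nothing about a prediabetes-range HbA1c.

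A second reply is that *or* means whichever test is available, and that fasting glucose is the glycemic measure the article names in the study blood work. On that reading discordance appears only when a chart holds a second value, and basing exclusion 4 on the test every participant has is a defensible feasibility choice in a pilot. This limits how often the problem can be seen. It does not say what to do when a second value is available and disagrees.

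A third reply is that the full protocol, available on request, may deal with discordant values. It may, but the published wording states a classification rule that is faulty as it stands. It is not a detail left out.

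**Conclusion.** The defect holds as a fault in stated eligibility wording and should be fixed. The two definitions are not mutually exclusive when measures disagree, and a person with intermediate HbA1c or OGTT and normal fasting glucose can enter the comparison group. The logical size is 31 of 54 profiles meeting both definitions, with 24 beyond the reach of exclusion 4.

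Three stronger readings are not supported.

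- **That dysglycemic people are entering the comparison group.** The documents give no rate of discordant results, so only *can enter* is justified. The 54 profiles are not equally likely and are not people.
- **That the power figures estimate the damage.** They rest on an assumed effect, an assumed share and an assumed outcome level in misclassified people. The protocol made no power calculation and acknowledges limited power. The figures show only the direction and a possible scale of dilution.
- **That every aim depends only on the group contrast.** Aim 3 and the exploratory aim also hypothesize pre-to-post change in both groups, and that change does not depend on clean group separation in the same way.

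The unknown frequency, the partial protection from documentation and the pilot purpose keep this below an essential correction.

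**What to change.** Reconcile inclusion criterion 6 with exclusion criterion 4, using the protocol's own cut-offs:

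1. Apply the T2DM definition first.
2. Define non-T2DM as no T2DM criterion met, including no drug used for hyperglycemia, and every available value (fasting glucose, OGTT, HbA1c) below its stated cut-off.
3. Apply the prediabetes exclusion to any available HbA1c or OGTT value as well as Part 2 fasting glucose. Keep the existing exception for documented, treated T2DM.
4. Re-check participants already enrolled against chart values where these exist. Recruitment began in March 2025 and is planned to late 2026, with baseline analysis from early 2026, so ideally this is done before that analysis.

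The cost is an IRB modification, some chart abstraction and possibly some additional screen failures. Chart review is already used for T2DM status and health history, but the article does not say that HbA1c or OGTT values are extracted, so the abstraction should be counted as new work. The remedy is partial: participants with no chart HbA1c or OGTT would still be classified on fasting glucose alone. The report should give the number classified on each basis.

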##### Cerebrovascular and Cognitive Function as Well as Cardiometabolic, Proinflammatory, and Epigenetic Outcomes

Part 2 of Baseline and Poststudy Testing involves participants coming to one of the study laboratories (Oklahoma City, Oklahoma) following an 8-hour fast, 12 hours of caffeine abstinence, and 24 hours of no alcohol, vitamins, other health supplements, or nonsteroidal anti-inflammatory drug use. They may continue taking medications aligned with health conditions. Participants are also required not to have exercised intensely in the last 24 hours. During this session, participants first complete blood pressure measurements and then blood and saliva sample collections. Blood samples are being collected through traditional venipuncture of the antecubital vein by trained study personnel. Samples are immediately processed and stored at –80 °C. From these blood samples, we assess high- and low-density lipoprotein and total cholesterol, and fasting blood glucose, among other outcomes, using the Lipid Panel+ kit of Piccolo Xpress (Abbott, Chicago, Illinois). Further, we will use enzyme-linked immunosorbent assays to assess high-sensitivity C-reactive protein as well as interleukin-6 and monocyte chemoattractant protein 1—analyses to be run nearer the end of the study to ensure minimal batch effects. These data will allow us to measure cardiometabolic and proinflammatory cytokines aligned with CICI and T2DM pathophysiology [10,11,21]. Finally, we collect saliva with a DNA Genotek OMNIgene Saliva DNA and RNA collection kit (OMR-610; Ottawa, Ontario). Participants spit 1 mL of saliva into the collection tube to a marked fill line, snap the tube closed, and provide it to research staff, after which it is stored at –80 °C. For the purposes of this study, genomic DNA isolations will be performed from whole blood and saliva for epigenetic analyses, namely, DNA methylation. Similar to the enzyme-linked immunosorbent assays, epigenetic analyses will also take place nearer to the end of the study in order to randomize samples to minimize batch effects.

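### The Part 2 fasting glucose that screens participants is also the pre-program glucose outcome, so regression to the mean in glucose change leans toward the T2DM hypothesis

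*Protocol article*

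**What the plan says.** Study Design and Recruitment (inclusion criterion 6) says that presence or absence of T2DM is "to be confirmed preferentially via physician’s documentation or via our measurement of participants’ fasting blood glucose", the latter being "fasting blood glucose during the blood draws within Part 2 of Baseline Testing". The fasting glucose route into the T2DM group is "current T2DM diagnosis as classified by a fasting blood glucose of ≥126 mg/dL"; a glucose tolerance test, HbA1c or medication use also qualifies. The matching route for the comparison group is "no current T2DM diagnosis as classified by a fasting blood glucose <100 mg/dL", again with alternatives.

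Exclusion criterion 4 is separate. It removes anyone "classified within the prediabetes range for their fasting blood glucose measurement (100-125 mg/dL) during Part 2 of Baseline Testing". The one exemption covers T2DM participants with physician documentation who also report medication or insulin and "who are found to be in the prediabetes range, will still be enrolled within the T2DM group and study".

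The outcome section on cerebrovascular, cognitive and cardiometabolic measures uses the blood drawn in that same session: "we assess high- and low-density lipoprotein and total cholesterol, and fasting blood glucose, among other outcomes". Part 2 is repeated at Poststudy. Statistical Analyses tests baseline group differences by t test and group differences in change by repeated measures ANOVA. Specific Aim 2 expects that "greater pre- to post-PA program improvements in these outcomes will be observed for cancer survivors with T2DM". Strengths and Limitations concedes that there is no true control group.

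**The concern.** One noisy measurement does two jobs: it screens people in or out, and it starts the clock for a change outcome. Taking the two eligibility rules together, a non-T2DM participant must read below 100 mg/dL at Part 2, because 100-125 is excluded and 126 or more meets a T2DM criterion. Some of those who pass do so because that day's reading fell below their usual level. At Poststudy no such filter operates, so the group mean returns upward. T2DM participants admitted on a single high reading return downward for the same reason.

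Both movements make T2DM participants look as if they improved more, which is the Aim 2 prediction. An untreated arm selected by the same rule would show the drift, but there is none. The ANCOVA fallback does not remove it, because that is triggered by sociodemographic or health differences. The baseline t test on glucose is also partly circular, since one side of the comparison is capped by rule. The study's stated purpose is to supply data for larger trials, so a biased glucose change would pass into their planning.

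**Working it through.** **The plan's own figure.** The article gives no number for this point. Its only sample-size figure is accrual: 30 / (1 - 0.20) = 37.5, rounded up to 38. That reproduces, and nothing below alters it.

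**Inputs from the article.** The cut-offs are <100 and ≥126 mg/dL, and the planned group size is 15.

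**Assumed inputs (not in the article).**
- Non-T2DM candidates: true mean 92-100, between-person SD 7-10, within-person SD 4-7 mg/dL.
- T2DM participants: true mean 130-140, between-person SD 25-30, within-person SD 8-15 mg/dL.
- Errors are normal and independent between visits, and there is no true change.

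**Formula.** Let μ be the true mean, b the between-person SD, w the within-person SD, s = √(b² + w²) and z = (cut-off - μ)/s. The expected apparent change is
- kept if below the cut-off: +(w²/s) × φ(z)/Φ(z)
- kept if at or above the cut-off: -(w²/s) × φ(z)/(1 - Φ(z))

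**Non-T2DM, kept if <100.**
- Smallest (92, 7, 4): s = 8.06, z = 0.992; (16/8.06) × 0.2438/0.8395 = **+0.58**.
- Largest (100, 7, 7): s = 9.90, z = 0; (49/9.90) × 0.3989/0.5 = **+3.949**, or 3.9.

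The share reading ≥100 at Poststudy runs from 8% to 33% over the same two cases. For the second, the correlation between visits is 49/98 = 0.5, so both readings fall below 100 with probability 1/3, and 1 - (1/3)/(1/2) = 1/3.

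**T2DM entered on a reading ≥126.**
- Smallest (140, 30, 8): s = 31.05, z = -0.451; (64/31.05) × 0.3604/0.6740 = **-1.10**.
- Largest (130, 25, 15): s = 29.15, z = -0.137; (225/29.15) × 0.3952/0.5546 = **-5.50**.

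**T2DM, documented and medicated.** No filter applies to the reading, so the expected drift is 0. Simulation gave -0.02 to +0.01.

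**Spurious group difference in change (size, favoring T2DM).**

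| T2DM participants who entered on the reading | mg/dL |
|---|---|
| none | 0.6 to 3.9 |
| all | 0.58 + 1.10 = 1.7, up to 3.949 + 5.50 = 9.4 |

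**Effect on the test.** With two visits, the group-by-time test is a t test on change. A separate simulation used 15 per group, an assumed two-sided 0.05 level, means of 95 and 135, SDs of 8 and 25, and no true change:

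| Within-person CV | none gated | half gated | all gated |
|---|---|---|---|
| 6% | 6.5% | 10.5% | 13% |
| 10% | 10% | 17% | 24% |

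These are false-positive rates, and nearly all of the rejections favor T2DM.

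**The case against.** The strongest reply is that documentation comes first. Group is set by the Part 2 reading only as a fallback, and medical records are checked whenever possible. That stands, and it limits the downward T2DM drift to an unstated and possibly small share. It does not remove the problem, because exclusion criterion 4 applies whatever the documentation and gives non-T2DM participants no exemption.

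A second reply is that the effect is small against the noise. Within-person variation alone gives the difference in change a standard error of √((2·4² + 2·8²)/15) = 3.3 to √((2·7² + 2·15²)/15) = 6.0 mg/dL, and the article already admits limited power. This also stands. The bias is modest, but it has one sign, and wide intervals do not correct it.

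A reader might infer that Aim 2 as a whole is biased. The documents do not support that. Aim 1's cardiometabolic hypothesis names blood pressure and insulin resistance, not glucose. Blood pressure, transcranial Doppler, cognition and cytokines are not selected on. Whether insulin resistance is affected depends on its computation, which the article does not give.

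A reader might also infer that the entry rules guarantee Aim 1's glycemic difference. They cap the non-T2DM group but set no floor for documented, medicated T2DM participants, and groups defined by diabetes status would be expected to differ in glucose anyway.

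**Conclusion.** The point holds for fasting glucose and for any measure calculated from the Part 2 value. The baseline is truncated by selection and the Poststudy value is not. The resulting artefact favors the hypothesis even if every T2DM participant is documented and medicated.

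Its size rests on the assumed means and variances, on independent visit errors, and on how many T2DM participants enter on the reading, which the article does not state. If documentation is the usual route, the lower range is the relevant one, and 9.4 mg/dL is a ceiling. It would be wrong to say that the reading decides group membership in general, or that the study's other outcomes are compromised.

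**What to change.** Treat the Part 2 glucose as an eligibility value. Report the baseline glucose difference and the group difference in glucose change descriptively, with a sentence on regression to the mean, and not as Aim 1 and Aim 2 hypothesis tests. Where a baseline glucose reading exists that was not used for eligibility, use it as the outcome baseline instead; with independent visit errors the expected artefact is then zero. State how insulin resistance is computed. If it uses the Part 2 glucose, keep it, since it is one of two named cardiometabolic hypotheses, and attach the same caveat to its change.

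The cost is that the fasting glucose contrast is no longer a hypothesis test, and a glucose-based insulin-resistance change must be read with caution. Descriptive reporting needs only a change in the analysis wording. Eligibility rules, the accrual target of 38 and all other outcomes stay as they are.
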